## 8 Phase 1 - Screening and Recruitment Phase

### 8.1 Telephone Contact

Once a reply sheet from a participant from Stream 1 (Annex 8.1) or Stream 2 (Annex 8.2) is received, they will receive an initial telephone call from the QIB Researcher. If a reply sheet is received from a participant from Stream 3 (Annex 8.3), they will receive the initial telephone call from a NSFT Research Nurse. Each participant will receive an overview of the study requirements and any questions will be answered. The Study Researcher will use the Telephone Contact section of the Telephone Contact/Pre-Study Visit Checklist (Annex 9) as a guide to providing all study information and checking eligibility before making the Pre-Study Visit appointment. It is anticipated that the Telephone Contact call will last approximately 20 minutes. If the participant is unsure of their medical history, they can check this with their GP and let the Study Researcher/NSFT Research team know before the Pre-Study Visit appointment is made.

If the participant has received antibiotics within 14 days, or a vaccination within 28 days of the planned Pre-Study Visit, the Pre-Study Visit will be delayed for the

appropriate washout period (antibiotics is 14 days from the date of the last dose and 28 days from the date of the last vaccination). This will ensure a baseline consistency at the point of consenting at the Pre-Study Visit. Any other circumstances which may delay the Pre-Study Visit from being booked will be discussed on an individual basis.

If the participant is not eligible to participate, they will be given the reason why and thanked for their time and interest in the study.

If the participant is eligible and is happy with the study requirements, the Pre-Study Visit appointment will be made.

For Stream 1 & 2, participants will attend the QI CRF. For Stream 3 participants, they will be seen in their own home by the NSFT Research Nurse as it is acknowledged that they would feel more comfortable. During the Telephone Contact discussion, the participant will be made aware that the Pre-Study Visit will last up to 2.5 hours and that during this time, the Study Researcher/NSFT Research Nurse will do the following: -

- ✚ Go through all elements of the study in full detail.
- ✚ Go through the Participant Instructions for Stool Collection (Annex 13) and the Participant Stool Sample Collection Log (Annex 14).
- ✚ Explain that the purpose of conducting the cognitive tests and associated questionnaires is designed so that memory, reasoning and thinking can be captured over the duration of the study. Show the participant a copy of the Full (Annex 16.1) and Partial Health Questionnaire (Annex 16.2).
- ✚ Explain the OCT (A) scans (Stream 2).
- ✚ Explain the brain MRI scans with the MRI checklist (Annex 17). The Study Researcher/NSFT Research Nurse will go through this checklist with all participants for consistency.
- ✚ Go through the Pre-Study Visit Checklist (Annex 9) to ensure all study information has been provided.
- ✚ Show the Data Collection Case Report Form (CRF) (Annex 18).
- ✚ Take Informed Consent (Annex 10) for the study and Biorepository Consent (Annex 11) for the long-term storage of samples.
- ✚ Explain and deliver the Cognitive test (mini-ACE) and associated questionnaire (CCI) and explain that the tests will form the final eligibility check for inclusion in to the study.
- ✚ Provide the Baseline Visit stool collection pack.

✚ Show and explain the Participant Withdrawal Postcard (Annex 29). If the participant decides to withdraw at any point during the study, they will be asked to complete and send the free post postcard and discard any contents of their collection pack.

The participant will be asked to bring any reading glasses for this appointment and will also be able to have someone accompany them if they wish. For all Study Visits to the QI CRF, mileage at 45p per mile will be paid and car parking charges will be waived. Any taxi or bus fares will be reimbursed upon production of a valid receipt.

## 8.2 Pre-Study Visit.

It is acknowledged that the Pre-Study Visit is a lengthy process (up to 2.5 hours) so the Study Researcher will schedule in regular comfort breaks that are convenient for the participant. The Study Researcher will follow the structure of this visit as described above.

The Study researcher will go through the consent form with the participant and encourage any questions they may have at this stage; after which the participant will sign the consent form agreeing to participate in the study.

After completing the Informed Consent process (see Sections 11.1), a copy of the completed Study Consent and Biorepository Consent (if applicable) (see section 11.2) will be given to the participant. Copies of all completed consent forms will be posted to the participant if the participant is from Stream 3.

Following completion of the Cognitive Test (mini-ACE) and the associated questionnaire (CCI), the participant will be provided with their Baseline Visit stool collection pack. See Section 11.3.1 for a full description of the Cognitive tests and associated questionnaires. It will be explained to the participant that within 5-10 working days, the anonymised Cognitive Tests will be scored by [name] or an experienced Research Assistant within his team, or a member of the Study Research Team to ascertain whether the participant is within the required threshold to be included in the study (see Section 11.3.1 for scoring thresholds).

The participant will then be contacted by the QIB Study Researcher to confirm their final eligibility, by telephone by prior arrangement. If their score does not fall within the required threshold, they will be thanked for their time and interest in the study

(Section 16). If the participant feels worried or anxious because they have any concerns, the Study Researcher will act sensitively and reassure the participant that the tests are for research purposes and are not indicative of any clinical diagnosis. Copies of the completed tests will be routinely sent to their GP (Annex 25) if the participant wishes to discuss them.

If the participant is not eligible to continue because the appropriate cohort for their score already has the required maximum number of 120 participants, they will be withdrawn from the study as per Section 16. Participants will be told that they did not reach the required threshold to be enrolled in the study, as they will not be aware of the cohorts. Arrangements will be made for the Study Researcher to pick up the stool collection pack.

If the participant is eligible to continue, an appointment will be made for their Baseline Visit at QI CRF. The Study Researcher will also discuss the OCT (A) scan appointment and brain MRI (if in cohort 3 and if applicable).

A summary of Phase 1 is shown in Figure 5.

[figure not shown]

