#### 5 STUDY DESIGN

The MOTION Study is an approximately 49-month longitudinal prospective study of 360 participants aged 60 years and over.

Participants will not have any severe medical conditions at baseline. By severe medical conditions we mean those that are known or are suspected to significantly affect either the gut microbiome or cognitive function. The rationale for the exclusion of severe medical conditions is that we want to be able to attribute changes in the dynamics of aging, particularly cognitive aging, to differences in the intestinal microbiota, and to describe the normal variation in microbiota (to which pathological changes or those induced by medications might later be compared). The presence of a baseline condition that would affect cognitive function by an

alternative process, for example untreated depression, would add variance to this outcome measure and make estimation of our associations of interest more difficult. See section 7.5 for the list of exclusion criteria.

The sample will be a convenience sample, selected through three different streams that together aim to identify participants from across the cognitive spectrum from healthy to those with mild cognitive impairment, while also enabling the collection of gut biopsies from a significant number through the course of their routine clinical care. While this is not a random sample and so will not be strictly representative of the population, there is little reason to expect that any particular selection bias will occur with respect to our research objectives.

Participants will be recruited via three streams (Primary Care as Patient Identification Centres, the NHS Bowel Cancer Screening Programme {BCSP} and the Norfolk & Suffolk NHS Foundation Trust {NSFT}) within the first two years to collect questionnaire and assessment data as well as biological samples at various time points. The research study will take place at the Quadram Institute Clinical Research Facility (QI CRF) where study visits will take place and QIB laboratory facilities. Additional study visits will be undertaken at the NNUH (QI Endoscopy, Imaging department) and Beccles Hospital.

A summary of the MOTION study design is detailed in Figure 2 below.

[figure not shown]

360 Study participants will be recruited using three streams: -

Stream 1 – Primary Care search of eligible participants.

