## 5.1 Cohorts

120 participants will be recruited in to each of the 3 cohorts as below.

- ❖ Cohort 1 – No subjective and no objective cognition deficit (low risk of developing dementia).
- ❖ Cohort 2 – Subjective but no objective cognitive deficits (medium risk of developing dementia).
- ❖ Cohort 3 – Subjective and objective cognitive deficits (high risk of developing dementia) recruited primarily through NSFT specialist clinical teams.

We would like to stress that the results of the cognitive tests are not clinically relevant but are only important for the purpose of this research. For this reason, results of the cognitive tests and stratification to one of the three cohorts will not be discussed with recruited participants as we do not wish to cause any undue anxiety or concern. In addition, this may also impact negatively on the study in

terms of participants either withdrawing themselves or altering their dietary and/or lifestyle behaviour.

The NSFT provided feedback from the Norwich Older Person's Forum regarding withholding information about a cohort they might be assigned to in a clinical trial. The attendees had no ethical concerns about the categorisation of participants in to groups was not clinically meaningful as they understood that assessments used in a trial alone and in the absence of a specialist clinician would have no relevance.

It is anticipated that all three cohorts may be populated from more than one stream. At the time of taking Informed Consent from the participant, it would not be known by the Study Researcher team which cohort the participant will be in. In the event of a cohort reaching its maximum number of 120 participants, the participant will be withdrawn as their scoring did not meet a required threshold for study entry in to any of the cohorts (see Section 16).

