### 10.1 Cognitive Tests

All cognitive tests and associated questionnaires will be sent to the participant's GP. Participants will be aware that the mini-ACE cognitive test is used as a tool in the clinical setting to diagnose dementia, but that it will only be used in combination with all other cognitive tests/associated questionnaires for research purposes. Copies of the mini-ACE and CCI test from the Pre-Study Visit will be sent to the participant's GP. The GP will also receive copies of cognitive tests and associated questionnaires taken at all the specified time points.

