## 16 EARLY TERMINATION/DISCONTINUATION/WITHDRAWAL OF PARTICIPANTS FROM STUDY

Each participant has the right to withdraw from the study at any time. In addition, the Investigator may discontinue a participant from the study at any time if the Investigator considers it necessary for any reason including:

- ❖ Cognitive test result at the Pre-Study Visit does not fall within the required threshold (Annex 26). This will also apply in the event of any cohort that already has the maximum number of 120 participants.
- ❖ Withdrawal of Consent (Annex 28).
- ❖ Ineligibility (either arising during the study or retrospectively having been overlooked at screening). See Section 7.5.
- ❖ Significant protocol deviation.
- ❖ Significant non-compliance with study requirements.
- ❖ Lost to follow up.

The reason for withdrawal will be recorded in the Study Withdrawal Log and the participant and their GP will be sent a Withdrawal Letter (Annex 27) from QIB explaining the reason for withdrawal. Participants who send their Study Withdrawal Postcard (Annex 29) will be sent a Participant Self-Withdrawal letter (Annex 28). Annexes 28 and 30 will explicitly state that the participant should contact the QIB Researchers if they wish to have any samples or data already collected to be destroyed, otherwise these will be included in the analysis.

Withdrawn participants or participants who withdraw themselves will not be replaced. In the event of Early Termination or Withdrawal, there will not be any additional visits.

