#### **Interim/monitoring analyses**

Interim reports will focus on monitoring the progress of the study against the main objectives to inform any necessary changes in protocol. These will include, as relevant at each stage of the study:

- Monitoring the rate of eligible participants from each stream,
- Participation rate of GPs
- Participation rate among different patient groups
- Rate of accruals from each stream
- Rate of accruals into each cohort
- Proportion consenting to each element of the study
- Demographic and clinical characteristics of the cohorts
- The completeness and quality of data and samples being received
- Patient's adherence to the sample collection protocols
- Response rate to sub-studies
- Attrition rate across different patient groups in each wave
- Rate of adverse events

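### People refused only because their cohort is full are to be told they missed the cognitive threshold, which is untrue under the protocol's own scoring rules

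*Protocol*

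**What the plan says.** Section 5.1 fixes the cohort sizes: "120 participants will be recruited in to each of the 3 cohorts as below". Cohort membership is not known at consent. It follows from the mini-ACE and CCI scores taken at the Pre-Study Visit.

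Section 8.2 deals with the person for whom "the appropriate cohort for their score already has the required maximum number of 120 participants". That person is withdrawn, and the instruction on what to say is: "Participants will be told that they did not reach the required threshold to be enrolled in the study". The justification given is that participants do not know about the cohorts. Section 5.1 describes the same event, a cohort at its maximum, and gives as the reason that "the participant will be withdrawn as their scoring did not meet a required threshold for study entry in to any of the cohorts".

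Section 16 lists a Pre-Study score outside the threshold as a ground for withdrawal (Annex 26) and adds in the same bullet that this also applies when a cohort is full. The reason is logged. The section also states that "the participant and their GP will be sent a Withdrawal Letter (Annex 27) from QIB explaining the reason for withdrawal".

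Sections 5.1 and 11.3.1 say that test results are not discussed with participants, so as not to worry them. Section 10.1 says: "Participants will be aware that the mini-ACE cognitive test is used as a tool in the clinical setting to diagnose dementia". The same sentence goes on to say that in this study the test serves research only, in combination with the other tests.

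**The concern.** A full cohort and a score outside every cohort's range are different reasons for not enrolling someone. The first is a matter of quota and says nothing about the person. The second is a statement about the person's test scores. The protocol gives the second reason in both situations.

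Participants will have been told that their tests are scored against a threshold as the final eligibility check, and they know that the mini-ACE has a clinical use in dementia. Being told that they did not reach the threshold is likely to be heard as a poor result. For a full-cohort refusal that is wrong, and it sits badly with a policy of withholding results to avoid distress.

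There is a smaller point about records. The interim reports in Section 19.1 include "Monitoring the rate of eligible participants from each stream", and those reports are meant to inform protocol changes. If full-cohort refusals are filed under the threshold reason, eligible people will look ineligible.

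**Working it through.** **Planned size.** Three cohorts of 120 give 3 × 120 = 360, which matches Section 5 ("360 Study participants will be recruited using three streams"). The caps are therefore exact. Unless all three cohorts fill together, anyone scoring into a filled cohort is refused while another is still recruiting.

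**Is the stated reason true?** The Section 11.3.1 rules applied to score pairs (mini-ACE out of 30; CCI on its first 12 questions):

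| mini-ACE | CCI | Result |
|---|---|---|
| 30 | 12 | Cohort 1 |
| 26 | 15 | Cohort 1 |
| 26 | 16 | Cohort 2 |
| 25 | 16 | Cohort 3 |
| 25 | 12 | no cohort |

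The two cut-offs make four combinations. Three are cohorts. Only mini-ACE < 26 with CCI < 16 fits none. The trigger in Section 8.2 is that the cohort appropriate to the score is full, so the person is in one of the three cohort cells and has met that cohort's threshold. The reason prescribed in Sections 5.1 and 8.2 is therefore false every time the full-cohort rule is used, including for a person scoring 30 and 12.

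**Is the protocol consistent on this?** Section 11.3.1 joins the two grounds with *or*, treating them as alternatives. Sections 5.1 and 8.2 state one in place of the other. Section 16 places both in a single bullet.

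**What could happen to the eligible rate?** The protocol gives neither of the numbers needed, so both are assumptions: S = people in range but refused because their cohort is full, and F = people fitting no cohort. Pooled over streams, with 360 enrolled:

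- true rate = (360 + S) / (360 + F + S)
- rate if full-cohort cases are logged as threshold failures = 360 / (360 + F + S)
- shortfall = S / (360 + F + S)

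| F | S | True | Logged | Shortfall (points) |
|---|---|---|---|---|
| 20 | 0 | 94.7% | 94.7% | 0 |
| 20 | 20 | 95.0% | 90.0% | 5.0 |
| 20 | 120 | 96.0% | 72.0% | 24.0 |
| 20 | 240 | 96.8% | 58.1% | 38.7 |
| 60 | 0 | 85.7% | 85.7% | 0 |
| 60 | 20 | 86.4% | 81.8% | 4.5 |
| 60 | 120 | 88.9% | 66.7% | 22.2 |
| 60 | 240 | 90.9% | 54.5% | 36.4 |

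The table shows direction and sensitivity only. The shortfall is zero if no one is refused for a full cohort, or if those cases have their own code.

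**The case against.** The best defence is that the vague wording protects the masking of cohorts, which Section 5.1 justifies by the risk of anxiety, withdrawal and changed behaviour. A message about filled places, given after scoring while advertising continues, might hint at score-based groups. That deserves care in the drafting, but it does not require an untrue statement. Section 5.2.2 already has participants told that 30 of the 360 will be offered MRI on the basis of their Pre-Study Visit results, so some link between scores and study arrangements is disclosed anyway.

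Several stronger readings are tempting and are not supported:

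- *The eligibility figures are corrupted.* What a participant is told need not be what is logged. The log's codes are not stated, Section 19.1 does not define eligible, scores are retained, and accrual into each cohort is monitored separately. Understatement is possible but not shown.
- *A withdrawal rate is inflated.* Section 19.1 lists attrition by patient group in each wave, not a withdrawal rate. Nothing says that people refused before Baseline enter that count.
- *The no-replacement rule in Section 16 does harm here.* It has no consequence, because a full cohort has no place to refill.
- *Anxiety will certainly follow.* It is a risk. Section 8.2 requires sensitive handling and reassurance that the tests are not diagnostic. That softens the message but does not correct it.
- *The GP is told that the person failed.* The wording of Annexes 26 and 27 is not shown, and the GP also receives the completed tests, so an in-range score would be visible.
- *The number affected can be estimated from an assumed Cohort 3 share.* Such a count treats recruitment as one unselected pool, whereas Section 5.1 expects Cohort 3 to come mainly through the NSFT specialist teams. The true number could be near zero.

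**Conclusion.** The point holds as a defect of wording and classification. Sections 5.1 and 8.2 prescribe a reason that is untrue whenever the full-cohort rule is applied, and Section 16 merges it with genuine threshold failures. This rests only on the protocol's own trigger and scoring rules. The conflict with the aim of avoiding undue anxiety is plain from the text, although actual distress is a risk and not a demonstrated effect.

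The number of people affected cannot be derived from the document. Any understatement of the eligible rate depends on how the log is coded. No objective, analysis or sample size is shown to be affected. The sponsor should nevertheless correct it, because the statement is false, concerns a cognitive test and is easily avoided.

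**What to change.** In Sections 5.1, 8.2 and 16, and in the matching letters:

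- Give full-cohort cases a true, neutral reason that reveals neither cohort nor score, for example that the available study places have been filled. Check that the wording stays accurate while another cohort is still open.
- Keep the threshold wording for scores outside all three ranges.
- Record *cohort full* and *outside thresholds* as two separate reasons for not enrolling.
- Count full-cohort cases as eligible when monitoring the eligible rate by stream.

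The cost is a few changes of wording, one extra reason code and a minor ethics amendment.

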## 9 Phase 2 - Sample and Data Collection Phase

Participants will be sent a standard reminder (by their preferred method) about their next Study Visit within one week in advance of their appointment (Annex 33).

They will also be reminded to bring a list of all their current prescribed and over-the-counter medication. The participant will be asked to let the Study Researcher know if they are taking or have taken antibiotics within one week of their scheduled appointment. In this case, the appointment will need to be rescheduled as a two-week washout is required from when the last dose of antibiotics was taken. In addition, they will also be reminded to let us know of any travel or flu vaccinations scheduled within 28 days of their appointment as a 28-day washout is required. The participant can record these on their Study Appointment Schedule (Annex 19). At the start of each study visit, the participant will be asked if they are still happy to continue with the study.

All study-related travel and car parking costs to QI CRF, NNUH and Beccles Hospital will be reimbursed to the participant at the end of each study visit. Mileage will be reimbursed at the current QIB standard rate of 45p/mile. Taxi and bus fares will be reimbursed on production of a valid receipt. Light refreshments and comfort breaks will be offered.

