### 3 OUTCOME MEASURES

| Objectives                                                                                                                                                                                                       | Outcome Measures                                                                                                                                                                     | Timepoint(s) of evaluation of this outcome measure (if applicable)                                                                                                                                 |
|------------------------------------------------------------------------------------------------------------------------------------------------------------------------------------------------------------------|--------------------------------------------------------------------------------------------------------------------------------------------------------------------------------------|----------------------------------------------------------------------------------------------------------------------------------------------------------------------------------------------------|
| 
Primary Objective
 
To describe how the gut microbiota changes over time in a cohort of individuals aged 60 years and older without existing serious health conditions on study entry.
 | 
Profile of the structure and composition of the bacterial component of the gut microbiota in a cohort of ageing individuals without serious health conditions.
                | 
Samples collected at start of study (t=0) and at 6 monthly intervals up to 48 months with sample analysis ongoing throughout the study.
                                                     |
| 
Secondary Objectives
 
1. Establishment of the study cohort and sample repository to facilitate future research into ageing.
                                                           | 
Successful recruitment to all three study groups.
 
Obtain all samples from individual participants according to procurement schedule. Deposit samples in Biorepository.
 | 
Recruitment completed within 24 months of study start date.
 
Sample repository initiated from study start date with further collections at 6 monthly intervals up to study end point.
 |

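### The antibiotic question before each stool visit looks back one week, but the washout it triggers is two weeks, so samples taken 8–13 days after a last dose can enter the primary outcome

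*Protocol*

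**What the plan says.** Section 9 of the protocol (Phase 2, covering Baseline and Study Visits 1–8) describes a reminder sent in the week before each visit. Participants are asked to "let the Study Researcher know if they are taking or have taken antibiotics within one week of their scheduled appointment". The consequence follows: "In this case, the appointment will need to be rescheduled", and the reason given is that "a two-week washout is required from when the last dose of antibiotics was taken".

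The same paragraph asks participants to report "any travel or flu vaccinations scheduled within 28 days of their appointment as a 28-day washout is required".

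Section 8.1 (Telephone Contact) sets the rule for the Pre-Study Visit. That visit is delayed if the participant "has received antibiotics within 14 days, or a vaccination within 28 days of the planned Pre-Study Visit", with washouts of 14 days after the last antibiotic dose and 28 days after vaccination.

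Section 3 makes the primary outcome the "Profile of the structure and composition of the bacterial component of the gut microbiota in a cohort of ageing individuals", with "Samples collected at start of study (t=0) and at 6 monthly intervals up to 48 months". That is nine stool samples per participant, all collected under the Section 9 rule.

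**The concern.** The interval that triggers rescheduling is half the length of the washout that rescheduling is meant to protect. Followed as written, Section 9 never prompts a participant whose last dose was 8 to 13 days before the visit, although that participant is still inside the stated washout.

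The rule controls every sample behind the primary outcome. Section 1.1 names drugs and medicines among the causes of change in the gut microbiome. The longitudinal questions in Section 19.1 include variation and trajectory within individuals, which depend on each person's samples being comparable. The Pre-Study Visit, where the question and the washout agree, is not a stool collection visit. The shorter question applies to the visits where stool is collected.

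**Working it through.** The protocol states no figure to reproduce here. The check is a comparison of the stated rules, a day count, and a scale calculation under a labelled assumption.

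**1. Rules side by side**

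| Rule | Interval asked about | Washout required | Difference |
|---|---|---|---|
| Pre-Study Visit, antibiotics (Section 8.1) | 14 days | 14 days | 0 |
| Phase 2 visits, vaccination (Section 9) | 28 days | 28 days | 0 |
| Phase 2 visits, antibiotics (Section 9) | 7 days | 14 days | 7 |

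Only the third rule has a question shorter than its washout, and no reason is given.

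**2. Day count**

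Let d be the whole days since the last dose. Day 7 counts as asked about and day 14 as washout complete. The gap is d > 7 and d < 14, so d = 8, 9, 10, 11, 12 or 13. That is 6 days, and 6/14 = 43% of the washout.

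**3. Other routes that might catch the exposure**

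- Medication list brought to the visit (Section 9): current medication only, so a completed course need not appear.
- Partial Health Questionnaire (Section 15.2.2): records medication use at follow-up visits. Section 21.1 also lists antibiotic use among the questionnaire data. No rescheduling rule is tied to either.

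These routes may record the exposure. Neither enforces the washout.

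**4. Scale**

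The documents give no rate of antibiotic use. Assume r courses per person-year, with course ends falling at random relative to visits and nobody in the gap volunteering the information.

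- Share of samples in the gap: p = r × 6/365.25
- Samples without attrition: 360 participants (Section 19.2) × 9 = 3,240
- Samples counting only the 300 participants whom Section 19.2 expects at the end: 300 × 9 = 2,700

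| Assumed r | p | Of 3,240 | Of 2,700 |
|---|---|---|---|
| 0.25 | 0.41% | 13 | 11 |
| 0.5 | 0.82% | 27 | 22 |
| 1.0 | 1.64% | 53 | 44 |

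Participants affected at least once over nine visits, treating visits as independent: 1 − (1 − p)^9.

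- r = 0.5: 1 − (1 − 0.0082)^9 ≈ 7%
- r = 1.0: 1 − (1 − 0.0164)^9 ≈ 14%

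**5. With the two intervals equal**

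If the interval asked about equals the washout, as in the other two rules, the gap is 0 days.

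**The case against.** The strongest reply is that Section 9 states the two-week washout without qualification and that the one-week period is only a prompt. On that view a sample taken on day 10 breaches the protocol; the protocol does not permit it. This stands as far as it goes. A reader might infer that such samples will enter the primary outcome, and the documents do not support that. A participant may mention an earlier course unprompted, or staff may learn of it on the day. The supported statement is that they can enter, because detection is too short for the requirement.

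A second reply is that exposure is meant to be recorded anyway. The questionnaires cover medication, and Section 11.1 provides for consent to access GP and hospital notes. This also stands in part. The data could support later adjustment, and since the questionnaires and forms are not shown, a new date field cannot be said to be needed. It does not close the sampling gap, because no rescheduling follows from those sources.

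A third reply is that the handling of exposed samples belongs in the analysis plans that Section 19.1 defers. That is right. The absence of an exclusion or flagging rule is not counted against the protocol.

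Finally, the number of affected samples is small under any of the assumed rates. That limits the consequence and leaves the contradiction in place.

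**Conclusion.** The point holds as an internal contradiction in a rule that governs all nine primary-outcome samples. The Phase 2 antibiotic question leaves 6 of the 14 washout days (43%) unasked, and nothing else in the protocol ties a rescheduled visit to an exposure in that interval.

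Under the assumed 0.25–1 course per person-year, roughly 0.4–1.6% of samples could be affected. At 0.5–1 course, about 7–14% of participants could be affected at least once. These figures rest on an assumed rate that the documents do not supply, and on nobody volunteering the information, so they indicate scale only. Sample size, power and the definition of the outcome are untouched.

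A reader might go further and infer that antibiotic exposure differs between the cohorts, or that the affected samples would imitate an effect of ageing. The documents do not support this. They give no antibiotic use by cohort or by frailty, and Section 11.3.1 defines the cohorts by mini-ACE and CCI scores. No distortion of the trajectories has been shown.

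The change is worth making because it costs little and a sample given inside the washout may not be replaceable for that time point.

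**What to change.** Reconcile Sections 8.1 and 9 so that the interval asked about before each stool visit equals the washout the protocol requires. If the reminder in Annex 33, which is not shown, carries the same wording, align it too. Which length is right is for the investigators to decide; this review does not propose one.

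The cost is a change of phrase. If the change lengthens the question, a few more visits will be rescheduled, and the window of one month either side in Section 9.1.4 can absorb them.
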